## 1. WHO Trial Registration Data Set

| Data category                                        | Information                                                                                                                                                                                                                                                                                                                                                                                                                                                                                                                                                                                                                                                                  |
|------------------------------------------------------|------------------------------------------------------------------------------------------------------------------------------------------------------------------------------------------------------------------------------------------------------------------------------------------------------------------------------------------------------------------------------------------------------------------------------------------------------------------------------------------------------------------------------------------------------------------------------------------------------------------------------------------------------------------------------|
| Primary registry and trial identifying number | ISRCTN43900695                                                                                                                                                                                                                                                                                                                                                                                                                                                                                                                                                                                                                                                               |
| Date of registration in primary registry      | 8 April 2020                                                                                                                                                                                                                                                                                                                                                                                                                                                                                                                                                                                                                                                                 |
| Secondary identifying numbers                 | Not applicable                                                                                                                                                                                                                                                                                                                                                                                                                                                                                                                                                                                                                                                               |
| Source(s) of monetary or material support     | Northumbria University                                                                                                                                                                                                                                                                                                                                                                                                                                                                                                                                                                                                                                                       |

| Contact for scientific queries                | [name]: contact details as above                                                                                                                                                                                                                                                                                                                                                                                                                                                                                                                                                                                                                                     |
| Public title                                  | Testing an early online intervention for the treatment of disturbed sleep during the COVID-19 pandemic (Sleep COVID-19)                                                                                                                                                                                                                                                                                                                                                                                                                                                                                                                                                      |
| Scientific title                              | Testing an early online intervention for the treatment of disturbed sleep during the COVID-19 pandemic (Sleep COVID-19)                                                                                                                                                                                                                                                                                                                                                                                                                                                                                                                                                      |
| Countries of recruitment                      | Worldwide                                                                                                                                                                                                                                                                                                                                                                                                                                                                                                                                                                                                                                                                    |
| Health condition(s) or problem(s) studied     | Acute insomnia                                                                                                                                                                                                                                                                                                                                                                                                                                                                                                                                                                                                                                                               |
| Intervention                                  | Online behavioural intervention                                                                                                                                                                                                                                                                                                                                                                                                                                                                                                                                                                                                                                              |
| Key inclusion and exclusion criteria          | 
Ages eligible for study: ≥18 years
 Sexes eligible for study: both
 Accepts healthy volunteers: yes
 Inclusion criteria:
 
 
Self-reported poor sleepers must meet DSM-5 criteria for acute insomnia.
 
Participants must have an adequate level of English comprehension.
 
 
Exclusion criteria: Individuals with reported chronic sleep disturbances, and those who are currently seeking treatment for their insomnia, and individuals with a self-history of head injuries, a self-reported diagnosis of schizophrenia, epilepsy or personality disorder.
 |
| Study type                                    | 
Study type: interventional
 Allocation: randomised
 Intervention model:
 Masking: single-blind (outcomes assessor)
 Primary purpose: treatment
                                                                                                                                                                                                                                                                                                                                                                                                                                                                     |
| Date of first enrolment                       | TBC (expected first enrolment August 2020)                                                                                                                                                                                                                                                                                                                                                                                                                                                                                                                                                                                                                                   |
| Target sample size                            | 60 (30 poor sleepers, 30 good sleepers)                                                                                                                                                                                                                                                                                                                                                                                                                                                                                                                                                                                                                                      |
| Recruitment status                            | Not yet recruiting                                                                                                                                                                                                                                                                                                                                                                                                                                                                                                                                                                                                                                                           |
| Primary outcome(s)                            | Insomnia Severity Index scores (post-intervention)                                                                                                                                                                                                                                                                                                                                                                                                                                                                                                                                                                                                                           |

|                                                            |                                                                                                                                                                                                                           |
|------------------------------------------------------------|---------------------------------------------------------------------------------------------------------------------------------------------------------------------------------------------------------------------------|
| Key secondary outcomes                              | 
 
• Subjective mood scores (PHQ-9 and GAD-7)
 
• Measures of sleep continuity derived from sleep diaries
 
• Insomnia Severity Index pre-post change scores
 
 |
| Study start date (date of initial ethical approval) | 8 April 2020                                                                                                                                                                                                              |
| Study end date                                      | 8 April 2022                                                                                                                                                                                                              |
| Study duration                                      | 24 months                                                                                                                                                                                                                 |

## 5. Funding

This study is financially supported by Northumbria University. This funding source has had no role in the design of this study and will not have any role during the execution of the study, in analyses and interpretation of data, or in decision to submit results.

## 7. Background

Theoretical models of insomnia suggest that psychophysiological arousal, due to a stressful life event, can cause a short-term disruption to sleep (i.e. acute insomnia) (Spielman, Caruso, & Glovinsky, 1987; Spielman, Nunes, & Glovinsky, 1996). Over time, this can result in an individual engaging in maladaptive compensatory behaviours, such as spending excessive time in bed and becoming preoccupied with sleep, creating a long-term problem of poor sleep through behavioural conditioning (Ellis, Gehrman, Espie, Riemann, & Perlis, 2012).

Previous naturalistic studies have indicated that stressful events, in the form of natural disasters such as earthquakes or hurricanes, or events such as war, can disrupt sleep (Askenasy & Lewin, 1996; Kato, Asukai, Miyake, Minakawa, & Nishiyama, 1996; Mellman, David, Kulick-Bell, Hebding, & Nolan, 1995; Seelig et al., 2010). The ongoing COVID-19 pandemic may represent one such stressful life event. However, early interventions may present an opportunity to prevent a short-term sleep disruption from becoming a long-term clinical sleep problem; specifically from becoming chronic insomnia (Ellis, Cushing, & Germain, 2015).

One non-pharmacological treatment, which is highly effective in the treatment of chronic insomnia, is cognitive behavioural therapy for insomnia (CBT-I). CBT-I is a structured psychotherapy which has the aim of changing maladaptive cognition and behaviours which contribute to the development of insomnia (Randall, Nowakowski, & Ellis, 2019). CBT-I results in equivalent improvements to those observed using pharmacological (hypnotic) treatments, with more durable after-effects following treatment discontinuation, and with concomitant reductions in symptoms of anxiety and depression (Riemann et al., 2017). For these reasons, CBT-I is recommended as a first-line treatment for chronic insomnia (Riemann et al., 2017). However, CBT-I may be too time and resource-intensive to be feasible and practical in the treatment of acute insomnia, and shorter interventions are likely to be of benefit.

One previous study, which used a self-help pamphlet alongside a 60-70 minute single (“one shot”) session of face-to-face CBT-I for acute insomnia, found that this method of treatment delivery was effective, on the basis of reductions on the Insomnia Severity Index (Ellis et al., 2015); follow-up studies have demonstrated efficacy when the treatment was delivered in a group format (Boullin, Ellwood, & Ellis, 2016) and in a male adult prison population (Randall et al., 2019). However, the use of the pamphlet alone, which is based on stimulus control, cognitive control, and imagery distraction techniques, will further increase the availability of brief interventions aimed at treating acute insomnia. Therefore, this intervention is well-suited to an online delivery model and can be used to reach a large number of people in the context of a large-scale stressful event. One potential limitation of the self-help pamphlet is that it is not yet known how long-lasting the effects of the intervention are. As such understanding this is necessary in order to maximise the efficacy of the intervention. Additionally, the use of such an intervention may aid the prevention of sleep problems in individuals with good sleep (i.e. where the intervention is used as a preventative tool).

Therefore, this study will examine if an online version of the self-help pamphlet is effective in reducing symptoms of acute insomnia in poor sleepers and determine if the effect is long-lasting, as well as investigate if the pamphlet is effective in the prevention of acute insomnia.

### **7.1. Choice of comparators**

The intervention in this study is an online version of a self-help leaflet, which outlines the principles of stimulus control, cognitive control and imagery distraction techniques. This leaflet is framed as being “3D’s”: ‘*Detect*’, which provides sleep diary instructions, ‘*Detach*’, which provides stimulus control instructions, and ‘*Distract*’, which refers to cognitive control and imagery distraction instructions.

This leaflet (Appendix 3) was originally developed to augment a single one-shot session of in-person CBT-I and has been successfully used in previous studies (Boullin et al., 2016; Ellis et al., 2015; Randall et al., 2019). Additionally, this leaflet, alone, has been shown to reduce cognitive and somatic arousal (Ellis et al., 2015).

Participants, who self-identify as poor sleepers in line with established criteria for acute insomnia, will receive the intervention. The comparator will be a wait-list control group of poor sleepers who will also receive the intervention, in addition to good sleepers who will receive the intervention, or who will not receive the intervention.

### **7.2. Study objectives**

#### *7.2.1. Primary objective*

The primary aim of the present study is to examine the efficacy of an online intervention for poor sleep in the context of an ongoing stressful major life event, by assessing if this intervention can reduce insomnia severity at short-term (one week post-intervention) and long-term (one and three months post-intervention) follow-up.

#### *7.2.2. Secondary objectives*

The secondary aims of this study are to: assess if the intervention can improve subjective anxiety and depression in poor sleepers, assess if the intervention can improve sleep continuity (derived from subjective sleep diaries), assess the effectiveness of the intervention (on the basis of effect sizes), and examine if the intervention can prevent the transition to acute insomnia in good sleepers.

### **7.3. Hypotheses**

It is hypothesised that the intervention will:

- 1) reduce insomnia severity in poor sleepers, compared to wait-list control poor sleepers, and good sleepers
- 2) reduce subjective symptoms of anxiety and depression in all groups.
- 3) prevent the transition to acute insomnia in good sleepers

## 8. Methods

### 8.1. Trial design

This study is designed as a cluster randomised controlled trial. Both self-reported good and poor sleepers will participate.

Good sleepers will be randomised into an intervention or a no intervention group, with a 1:1 allocation. Poor sleepers will be randomised into an intervention or wait-list control (i.e. where they will receive the intervention after a delay) group, with a 1:1 allocation. Overall, poor and good sleepers will participate at a 1:1 ratio (Figure 1).

[figure not shown]

NB: good sleeper participants who do not receive the intervention will complete the follow-up stages at an equivalent time point.

Figure 1: participant flowchart

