#### *8.9.3. Intervention*

Poor sleepers will receive the intervention after the one-week baseline period. Poor sleepers who are wait-list controls will receive the intervention after a delay of one month (28 days), and will extend their monitoring period accordingly, with extra ISI, GAD-7, PHQ-9 and PSS measures to be completed on Day 28 (Figure 2).

Participants will repeat the ISI, GAD-7, PHQ-9 and PSS immediately prior to receiving the intervention.

Good sleepers, who will receive the intervention, will do so at the same time as poor sleepers (Figure 2). Good sleepers who do not receive the intervention will follow an identical timeline to the poor sleepers who do receive the intervention (Figure 2).

Assessments will be modified at Day 8 (or the equivalent time point where appropriate) to only ask about the previous week.

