#### *8.9.5. Follow-up periods*

At one week follow-up (i.e. one week after the intervention), or an equivalent time point for good sleeper participants who do not receive the intervention, participants will complete the KSS, GAD-7, PHQ-9 and ISI. At one month and three months follow-up, participants will complete the KSS, GAD-7, PHQ-9, SF-36, MADRE and ISI. Participants will receive a debrief (Appendix 4) at the end of the study.

Assessments will be modified at follow-up points to only ask about the previous week, with the exception of the SF-36, which will not be modified.

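### On the available text, wait-list poor sleepers have no untreated ISI at the time of the treated arm's one-week follow-up, so the short-term primary objective lacks a same-time randomised comparison

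*Combined protocol and SAP*

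**What the plan says.** Section 7.2.1 sets the primary aim as finding out whether the leaflet can "reduce insomnia severity at short-term (one week post-intervention) and long-term (one and three months post-intervention) follow-up". Hypothesis 1 in Section 7.3 is that it will "reduce insomnia severity in poor sleepers, compared to wait-list control poor sleepers, and good sleepers". Under Section 8.1, poor sleepers are randomised 1:1 between the leaflet and a wait-list, so the wait-list arm is the only randomised comparator for treated poor sleepers.

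On timing, Section 8.9.3 states: "Poor sleepers will receive the intervention after the one-week baseline period". The wait-list arm has the leaflet after a 28-day delay, "with extra ISI, GAD-7, PHQ-9 and PSS measures to be completed on Day 28". Everyone who receives the leaflet also repeats the ISI just before it.

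The note to Figure 1 in Section 8.1 says that "good sleeper participants who do not receive the intervention will complete the follow-up stages at an equivalent time point". Section 8.9.5 counts the one-week follow-up from the leaflet, "or an equivalent time point for good sleeper participants who do not receive the intervention". Table 1, which Section 8.9 presents as the complete list, has the ISI at baseline, pre-intervention and the one-week, one-month and three-month follow-ups. It has no separate wait-list column.

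Section 10 analyses the ISI with a 4 x 5 mixed ANOVA. Its five time levels are baseline, pre-intervention and the three follow-ups, the last four of them placed relative to the intervention.

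**The concern.** To learn what the leaflet does within a week, one needs untreated poor sleepers measured at the same time since randomisation as the treated ones. The plan arranges this for untreated good sleepers. No such arrangement can be found for the wait-list arm, although that arm is untreated at the time.

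A score that was never collected cannot be recovered by recoding time in the analysis. What remains is either to pair ISI scores from different days, or to rely on the planned ANOVA, which sets treated poor sleepers against poor sleepers who by then have also been treated. In both cases, any change in poor sleepers that has nothing to do with the leaflet enters the estimate for the first-named hypothesis.

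**Working it through.** The plan gives no figure for this point. Its sample size (48 evaluable, 60 recruited, Section 8.6) is not affected. The check is a calendar.

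**1. Inputs.** Baseline is taken as Day 0. The treated arm's leaflet comes after the one-week baseline period, at about Day 8 (Section 8.9.3). One week is 7 days. One month is taken as 28 days, as Section 8.9.3 does for the delay. Three months is taken as 84 to 90 days. The text does not say from which day the 28-day delay runs, so each reading is shown.

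**2. ISI days in the two poor-sleeper arms.**

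| Arm | Untreated ISI | ISI after the leaflet |
|---|---|---|
| Treated, leaflet about Day 8 | 0, 8 | 15, 36, 92 to 98 |
| Wait-list, leaflet Day 28 | 0, (8), 28 | 35, 56, about 112 |
| Wait-list, leaflet Day 35 or 36 | 0, (8), 28, 35 or 36 | 42 or 43, 63 or 64, about 119 or 120 |

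The Day 8 wait-list score is in brackets because the text leaves it open.

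**3. The gap.** The treated one-week score is at 8 + 7 = Day 15. No reading puts a wait-list ISI on Day 14 or 15. The next untreated wait-list score is on Day 28, which is 28 - 15 = 13 days later. The treated arm has no Day 28 score to set beside it.

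**4. What each comparison estimates.** Let c(t) be the mean ISI change from baseline to Day t in untreated poor sleepers, and d the leaflet effect at one week. Assume that the two add and that d is the same whenever the leaflet is given.

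- Same time, not collected: [c(15) + d] - c(15) = d.
- Treated Day 15 against untreated wait-list Day 28: [c(15) + d] - c(28) = d + c(15) - c(28).
- Section 10, one-week level: [c(15) + d] - [c(35) + d] = c(15) - c(35) with the leaflet at Day 28. With the leaflet at Day 36, c(43) replaces c(35).

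In the third line d cancels. The contrast between the two poor-sleeper arms at that level then carries only the difference in calendar time, 35 - 15 = 20 to 43 - 15 = 28 days. If the effect differs with the time of delivery, d cancels only in part.

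**5. Illustrative size.** The documents give no rate of change in untreated poor sleepers. If it were a steady fall of r points per week, c(15) - c(28) = r x 13/7:

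- r = 0.25: 0.25 x 13/7 = 0.46 points
- r = 1.0: 1.0 x 13/7 = 1.86 points

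With falling scores, pairing Day 15 with Day 28 would understate a benefit. With rising scores it would overstate one.

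**The case against.** **Figure 2 is not available.** Section 8.10 calls it the detailed timeline for each participant group, and it may show more than the text. Neither Section 8.1 nor Section 8.9.5 says that only good sleepers have the equivalent-time follow-up. This stands as a limit on certainty. Against it, Section 8.9.3 cites Figure 2 in the very sentence that names Day 28 as the extra assessment, so a Day 15 ISI there would go beyond the text and Table 1.

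**The untreated scores bracket Day 15.** Under steady change, baseline (or Day 8) and Day 28 could be interpolated to Day 15 without bias. That is right, and so 0.46 to 1.86 points is not an unavoidable error. But interpolation depends on the assumed shape, and Section 10 does not plan it.

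**Other same-time data exist.** Untreated good sleepers have an ISI at the matching time and are a named comparator. The wait-list arm extends its monitoring, which in Section 8.9.2 means sleep diary, state anxiety and sleepiness. Good sleepers are a different population, not randomised against poor sleepers, and the daily measures are not the ISI.

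**The one-month point may be covered.** If the wait-list leaflet comes on Day 35 or 36, that arm's pre-leaflet ISI falls within about a day of the treated arm's one-month score. This serves the one-month aim, not the one-week aim.

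**The gain is modest.** With 48/4 = 12 completers per arm and an assumed standardised difference of 0.5, an unadjusted two-sided 5% t-test has about 22% power even with a same-day comparison. That is a limit of the sample size, not a reason to leave the comparison without its control score.

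**Conclusion.** On the available text, the wait-list arm has no ISI while untreated at the time of the treated arm's one-week follow-up. The short-term primary objective therefore has no same-time randomised untreated comparison, and the planned ANOVA puts a post-leaflet wait-list score in its place. This rests on Sections 8.1, 8.9.3 and 8.9.5 and Table 1, subject to Figure 2. It does not depend on any assumed recovery rate.

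Three stronger readings are tempting and are not supported.

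- A reader might infer that the wait-list arm has no untreated ISI after baseline. It has one on Day 28.
- A reader might infer a known bias, or a known loss of power or rise in false positives. Any such figure needs a recovery rate that the documents do not give, and pairings of different days that Section 10 does not plan. The 0.46 to 1.86 points are an illustration only.
- A reader might take the leaflet in Appendix 3 as saying that untreated sleep simply recovers. Its statement depends on the stress ending or the person coping with it, and the same page says that insomnia can persist once the stress is under control. Section 7 describes the pandemic as ongoing. The direction of change without treatment is therefore open.

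This is a cheap improvement that is best made before enrolment, since the score cannot be obtained afterwards.

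**What to change.** First check Figure 2. If it already schedules a wait-list ISI at the treated arm's one-week point, bring the text and Table 1 into line with it. If not:

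1. In Sections 8.9.3 and 8.9.5 and in Table 1, add the ISI, GAD-7 and PHQ-9, with previous-week wording, for wait-list poor sleepers at the time equivalent to the treated arm's one-week follow-up (about Day 15). Extend the equivalent-time wording in Sections 8.1 and 8.9.5 to that arm.
2. In Section 10, define the short-term poor-sleeper comparison as treated against still-untreated wait-list at that same time since randomisation, adjusted for baseline ISI. Without this the new score has no place in the five-level ANOVA and the primary test would not change.
3. Optionally, add a Day 28 ISI in the treated arm, so that the wait-list Day 28 score has a same-day partner.
4. State the day from which the 28-day delay is counted, so that the calendar can be read one way. The timing of the leaflet need not change.

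The cost is one short online questionnaire set in about 15 participants (about 30 participants affected if the Day 28 ISI is added), a change to the Qualtrics set-up and a protocol and ethics amendment under Section 13. The downside is one more self-rating occasion. The registration data set lists the trial as not yet recruiting.
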